### Data collection

We will collect outcomes relating to four levels of specification of outcome measures as proposed by Zarin et al. [25]: domain (for example, postoperative delirium); specific metric (for example, RASS); specific metric used to characterize each participant’s results (for example, the incidence within the seven-day period after surgery); and method of aggregation (for example, mean change and 95% confidence interval).

A research assistant will collect date elements from patient medical records, including:

Demographic data:> data of birth;> gender;> preoperative diagnosis;> previous treatments;> co-morbid conditions;> preoperative vital signs: pulse (P), BP, respiratory rate (R);> baseline laboratory tests: aspartate transaminase (AST), alanine aminotransferase (ALT), blood urea nitrogen (BUN), serum creatinine (CREA), C-reactive protein (CRP), creatine kinase (CK), creatine kinase isoenzymes (CK-MB), brain natriuretic peptide (BNP), HB, white blood cell (WBC), platelet (PLT), oxygenation index (PaO_2_/FiO_2_), arterial carbon dioxide pressure (PaCO_2_), total bilirubin and fractions, prothrombin time (PT), activated partial thromboplastin time (APTT), international normalized ratio (INR);> preoperative electrocardiogram;> the ASA classification for preoperative health assessment of surgical patients [26].

Operative information:> name of surgical operation;> participation of fellow, resident, or medical student/clinical clerk in the surgical team;> intraoperative blood loss;> transfusion of blood products (packed red blood cells, platelets, fresh frozen plasma, albumin) and number of units;> volume of intravenous crystalloid infusion;> intraoperative urine volume;> intraoperative drug dosage, including in urapidil, phenylephrine and fursemide;> duration of surgery (defined as the number of hours between skin incision and closure of skin).

### Laboratory analyses

Preoperative values of laboratory tests (AST, ALT, BUN, CREA, CRP, CK, CK-MB, BNP, HB, WBC, PLT, PaO_2_/FiO_2_ and PaCO_2_) performed within the last week before surgery will be used as baseline values (before surgery). Additional blood samples will be collected on postoperative day 1 for serial laboratory evaluation.

### Postoperative complications

An independent board-certified physician will be the outcome assessor. He will be instructed about diagnostic criteria for specific postoperative complications in this trial. The outcome assessor will evaluate all participants until 28 days after surgery.

Diagnostic criteria for specific postoperative complications:> postoperative cognitive impairment defined by the confusion assessment method for the intensive care unit (CAM-ICU) [27]. First, level of sedation (level of arousal) was assessed using the RASS. If the patient was deeply sedated or was unarousable (– 4 or – 5 on the RASS), then assessment was stopped and repeated later, and the patient was noted as comatose. If RASS was > – 4 (– 3 through + 4), then assessment was continued to the next step. Second, delirium was diagnosed using CAM-ICU. It detects four features of delirium: acute onset of mental status changes or a fluctuating course; inattention; disorganized thinking; and altered level of consciousness. To have delirium diagnosed, a patient must display the first two aforementioned features, with either the third or fourth aforementioned feature;> hemorrhage: if requiring reoperation, radiological or endoscopic intervention; information on postoperative transfusion of blood products (type and number of units) will also be collected;> arrhythmias: any change in cardiac sinus rhythm prompting specific medical intervention or patient transfer to a monitored bed;> pulmonary embolism: confirmed by computed tomography (CT);> deep venous thrombosis: confirmed by Doppler ultrasonography;> acute liver failure: confirmed by physical exam, laboratory findings, patient history, and past medical history to establish mental status changes, coagulopathy, rapidity of onset, and absence of known prior liver disease, respectively [28];> acute kidney injury: defined by the Kidney Disease: Improving Global Outcomes (KDIGO) creatinine-based criteria [29];> all cases of acute myocardial infarction, cerebrovascular accident, or transient ischemic attack, as diagnosed by appropriate medical specialist;> other: any unlisted postoperative complications requiring specific medical treatment, radiological intervention or reoperation.

### Study outcomes

Primary outcome measure:

The incidence of PD within the seven-day period after surgery. Patients will be assessed for delirium with the CAM-ICU twice daily (at 08:00–10:00 and 18:00–20:00) during the first seven days after surgery.

Secondary outcomes:Delirium duration days during the seven-day period after surgery.Intraoperative urine volume.Intraoperative blood loss: estimated using loss of red cell mass, which was derived from differences in pre- and postoperative hematocrits and transfused red cell mass with the following equation [30]: loss of red cell mass (mL)  =  estimated blood volume of patient (mL)  ×  (preoperative hematocrit (%) − immediate postoperative hematocrit (%))/100 + (transfused packed RBCs [unit]  ×  213  ×  0.7) (estimated blood volume of patient [mL]  =  75 mL/kg for men or 65 mL/kg for women  ×  body weight [kg]; 213 mL for average volume of packed RBC; 0.7 value for hematocrit of packed RBCs).Specific postoperative complications within the seven-day period after surgery, including in bleeding requiring intervention, arrhythmias, pulmonary embolism, deep venous thrombosis, acute liver failure, acute kidney injury, acute myocardial infarction, cerebrovascular accident, or transient ischemic attack.All-cause 28-day mortality.

### Adverse events

Serious adverse events and other untoward events that require hospitalization, are life-threatening, or result in death are collected following the SPIRIT recommendations [21]. All adverse events will be recorded and closely monitored until resolution or stabilization or until it has been shown that the study treatment is not the cause of the event. The Chief Investigator will be informed immediately of any serious adverse events and will determine (in cooperation with the treating medical practitioners) the seriousness and causality of these events. All treatment-related serious adverse events will be recoded and reported to the research Ethics Committee as part of the report. Unexpected serious adverse events will be reported to the research Ethics Committee within the relevant time frames. The Chief Investigator will be responsible for all adverse event reporting. All site staff will be appropriately trained in the procedures to follow and the forms to use during the study protocol before study initiation. If serious side-effects occur, the Chief Investigator can then unblended the participant and give the patient post-trial care.

### Withdrawal and dropout

Participation in the study will end at any stage if the patient refuses to continue, withdraws consent, or violates inclusion or exclusion criteria or the trial protocol. The trial will be stopped if the principle investigator believes that there are unacceptable risks of serious adverse events. No interim analysis will be conducted; however, the Data Safety and Monitoring Committee (DSMC) will perform regular reviews of all study outcome and adverse event data to ensure that there is no difference in rates of hospitalization or exacerbation in either group. The DSMC will determine final criteria for early study termination, which may be based on clear-cut evidence of worsened safety in one of the trial arms, and in the case of evidence beyond reasonable doubt of clear-cut benefit in the primary outcome measure, an effect size which would change clinical practice in the presence of the current literature and understanding of the disease area.

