### Patient population and eligibility criteria

Patient eligibility is assessed at the preoperative anesthesia consultation. All eligible patients must sign a specifically designed informed consent form.

Inclusion criteria are: men and women; American Society of Anesthesiologists (ASA) I–II; aged 65 years or more; scheduled to undergo non-cardiothoracic surgery with GA; and 2 h or more of scheduled surgery time.

Participants will be excluded if they meet any of the following conditions: (1) the patient suffered from cardiovascular disease and metabolic diseases, such as hypertension, cardiac diseases, diabetes; (2) the patient has severe liver, kidney, or blood disease; (3) the patient is accompanied severe cognitive impairment (Mini-Mental State Examination [MMSE] score < 15) [22]; (4) preoperative history of schizophrenia, epilepsy, parkinsonism, use of cholinesterase inhibitor, or levodopa treatment; use of haloperidol or other neuroleptics during or after anesthesia; (5) neurosurgery; (6) individuals unlikely to survive for > 24 h; (7) previous participation in this study.

Trial schematic diagram is shown in Fig. 2.

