### Randomization and blinding

Once consent is provided, participants will be assigned by the research assistant to either the low-level MAP group or high-level MAP group according to a random allocation sequence. An online random list generation will be utilized to perform blocked randomization in a 1 : 1 ratio. Trials cannot be blinded to anesthesiologist because anesthesiologist must know the MAP target to which each participant has been assigned in order to make the proper adjustment in the therapy to achieve 60–70 mmHg or 90–100 mmHg MAP. Outcome assessment and statistical analyses will be performed by independent researchers. Outcome assessor and the surgical team will be blinded to the study allocation status of participants.

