### Intervention

On the day of surgery, patients come to the operating room and are provided with standard monitoring (electrocardiogram, oxygen saturation, non-invasive blood pressure, and invasive pressure monitoring). GA is given using midazolam (0.04 mg.kg^–1^) and propofol (as deemed appropriate by the anesthesiologist), opioids (fentanyl 3–6 μg.kg^–1^ and remifentanil 0.1–0.5 μg.kg^–1^.min^–1^), muscle relaxants (cisatracurium/rocuronium), and maintained with sevoflurane with inhaled concentrations of 1.5% sevoflurane in oxygen. Supplemental dosing of 1 μg.kg^–1^ of fentanyl is used every hour from induction up to approximately 1 h prior to the end of surgery. A tramadol bolus of 2 mg.kg^–1^ is given 15–30 min before the end of surgery. Propofol infusion is stopped 5–10 min before the end of surgery, whereas at the end of skin closure, remifentanil was discontinued.

According to grouping, MAP is regulated to the goal level (60–70 mmHg or 95–100 mmHg) during GA. If necessary, intravenous anti-hypertensives (urapidil [0.2–0.5 mg.kg^–1^] or phenylephrine [4–6 μg.kg^–1^] when MAP exceeds 10 mmHg of the target value), rather than more anesthesia, may be used in situations wherein sympathetic stimulation is high; yet a sufficient amount of anesthesia is administered and bispectral index (BIS) shows an adequate depth of hypnosis. Sedation is provided by a propofol infusion targeted to a BIS number of approximately 50 during GA. Atropine (5–10 μg.kg^–1^) and esmolol (1–3 mg.kg^–1^) would be used at the time of heart rate < 50 beats.min^–1^ and > 110 beats.min^–1^, respectively.

Lactated Ringer’s solution is given to bring the maintenance fluids to 10 mL.kg^–1^.h^–1^ [23]. Blood loss could be corrected for in a 1 : 1 ratio using gelofusine. Hospital transfusion guidelines are used to determine whether blood products are necessary (hemoglobin [HB] level < 10 g.dl^–1^ in patients with cardiac co-morbidities and < 7 g.dl^–1^ in those without cardiac disease). For later starting cases, an additional bolus of Ringer’s solution of 1.5 mL/kg/fasted hour from 08:00 _i_s given to bring the total to 2 mL/kg/fasted hour. If urine output decreases to < 0.5 mL.kg^–1^.h^–1^ for 1 h, fursemide 0.3 mg.kg^–1^ is given.

Mechanical ventilation patterns are adjusted to obtain an end-tidal carbon dioxide value of 35–45 mmHg at 5–10 min after induction of anesthesia.

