### Statistical analysis

Postoperative delirium is a frequent complication after major surgery in elderly patients and is related to an increase in mortality [31]. Probability of first postoperative day PD in elderly hip fracture patients is in the range of 20–60% [9]. PD occurred in 44% of elderly patients after a major operation [31]. Our sample size was calculated to detect a 15% difference in PD between the two groups with a two-tailed test, a significance level (alpha) of 5%, and a power of 80%. The sample size calculation was performed on STATA 14.0 software (StataCorp, College Station, TX, USA). We plan to include a total of 322 participants.

Analyses will be conducted at the Clinical Research Institute of Shenzhen People’s Hospital by blinded biostatisticians. Data analysis is on an intention-to-treat basis.

The level of significance was set at 5% and statistical analysis was performed using GraphPad Prism version 6.02 for Windows (GraphPad Software, San Diego, CA, USA). Continuous variable will be summarized using means and SDs (normally distributed data) or medians and ranges (non-normally distributed data). We will perform group comparison by using the Student’s t test or Mann–Whitney test for quantitative variables and Pearson’s chi-squared test for categorical variable. The odds ratio and 95% confidence interval will be computed with logistic regression.

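### The withdrawal rule ends participation on any eligibility or protocol violation, so the outcomes that the promised intention-to-treat analysis needs may not be collected

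*Protocol article*

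**What the plan says.** Under Withdrawal and dropout, the protocol article stops participation, whatever point has been reached, for a patient who declines to go on, takes back consent, "or violates inclusion or exclusion criteria or the trial protocol". Violations thus stand beside refusal and withdrawn consent. No degree of severity is set, stopping the intervention is not distinguished from stopping follow-up, and nothing says that outcomes are still collected afterwards.

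Under Statistical analysis: "Data analysis is on an intention-to-treat basis".

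Four other places bear on how these two statements meet:

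- Study outcomes defines the primary outcome as "The incidence of PD within the seven-day period after surgery", assessed twice a day. All-cause mortality at 28 days is a secondary outcome.
- Randomization and blinding: "Once consent is provided, participants will be assigned by the research assistant". The treating anesthesiologist knows the arm: "Trials cannot be blinded to anesthesiologist because anesthesiologist must know the MAP target".
- Patient population and eligibility criteria lists among the exclusions "use of haloperidol or other neuroleptics during or after anesthesia".
- Postoperative complications has the outcome assessor evaluate all participants up to day 28.

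**The concern.** Intention to treat needs two things: every randomized patient stays in the assigned group, and every patient's outcome is sought. The statistical section promises the first. The withdrawal rule, taken literally, undoes the second for anyone with a violation. A patient whose participation ends in the operating room has no postoperative delirium assessment. One whose participation ends on day 2 has an incomplete seven-day record and possibly no 28-day status. No later analysis plan can recover assessments that sites were told to stop.

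The loss need not be random. The core instruction of the trial is an arm-specific pressure range delivered by an unblinded clinician, so the number and kind of recorded violations could differ by arm. Neuroleptic use after anesthesia is written as an exclusion criterion although it can arise after randomization, and it may be a response to delirium. Under the withdrawal rule, the primary event could therefore trigger the end of participation.

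**Working it through.** **1. The plan's own sample size.** Inputs from Statistical analysis: 44% delirium (a cited rate, not explicitly named as the control rate), a 15% difference, two-sided 5% level, 80% power. The 1:1 ratio is under Randomization and blinding. Reading the difference as 44% against 29%, with pooled rate 0.365:

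n per arm = [1.960·√(2·0.365·0.635) + 0.842·√(0.44·0.56 + 0.29·0.71)]² / 0.15² = 160.5, rounded up to 161, or 322 in total.

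This matches the stated total exactly, and power at 161 per arm is 80.1%. An allowance for 5% loss would have given 322/0.95 = 339, and for 10% loss 322/0.90 = 358. The figure of 322 therefore contains no allowance.

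**2. Power if violations cost outcome data.** The loss rates are assumptions, equal in both arms and unrelated to risk.

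| Loss | Patients with outcome | Power, 44% vs 29% |
|---|---|---|
| 0% | 322 | 80.1% |
| 5% | 306 | 78.1% |
| 10% | 290 | 75.8% |

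**3. Bias if the loss is selective.** Assume no true effect (44% in both arms), with a fraction v of one arm losing its outcomes and delirium risk r among those lost. The rate among the remaining patients is (0.44 − v·r)/(1 − v). The rejection probability uses the normal approximation, with 161 patients in the intact arm and 161·(1 − v) in the other. With r = 65%:

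| v | Remaining rate | Spurious difference | Rejection |
|---|---|---|---|
| 5% | (0.44 − 0.0325)/0.95 = 42.9% | 1.1 points | 5.4% |
| 10% | (0.44 − 0.065)/0.90 = 41.7% | 2.3 points | 7.0% |
| 20% | (0.44 − 0.13)/0.80 = 38.75% | 5.25 points | about 15% |

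Two settings give no bias: r = 44% (those lost carry average risk), and the same v and r in both arms. The range therefore starts at zero. The largest value shown is about a third of the 15-point design difference (5.25/15 = 0.35). The document supplies neither v nor r.

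**4. Is the link to arm or outcome in the text?**

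- Outcome: the neuroleptic exclusion covers use after anesthesia, so it can be met after randomization. If delirium was recorded first and that record is kept, the primary event survives, but delirium duration is cut short and 28-day status may be lost. If the drug comes before a positive assessment, the primary outcome itself may be missing.
- Arm: the targets differ by arm and the anesthesiologist is unblinded. The Intervention section also says "MAP is regulated to the goal level (60–70 mmHg or 95–100 mmHg) during GA", while the abstract, Trial design and Randomization and blinding give 90–100 mmHg for the high arm. If an off-target pressure were counted as a violation, the count in that arm alone would depend on which range is applied. These passages must be reconciled.

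**The case against.** The withdrawal section says that participation ends. It does not say that collected data are discarded or that patients leave the analysis set, and intention to treat is stated without exceptions. The assessor is to evaluate all participants to day 28, and adverse events are followed until they resolve or stabilize, or are shown not to be caused by the treatment. On this view the passages are in tension, and a sentence of clarification is enough.

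Part of this stands. A reader might infer that the trial would be a per-protocol comparison in all but name, with sicker patients deleted from one arm. The text does not say so. A reader might also take a missed pressure target to be the main violation. No passage defines it as one, the Intervention section provides drug treatment for excursions, and the rule speaks of what the patient violates. Nor does any passage say which target is harder to hold, so a bias in favor of a particular arm cannot be claimed. Enrollment is limited to ASA I–II patients without cardiovascular or metabolic disease, which may keep violations few.

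What does not stand is that the other passages cure the rule. Follow-up of all participants does not clearly reach someone whose participation has ended. Adverse-event monitoring does not replace twice-daily delirium assessment. Reading the rule as patient non-compliance alone does not fit its eligibility limb, and seven centers could apply an unqualified rule in different ways. This is a stated rule, not a detail left out of a condensed article.

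**Conclusion.** The concern holds in this form: the withdrawal rule, followed as written, stops collection of outcomes that the stated intention-to-treat analysis requires, so that analysis could not be done in full for patients with a violation. The loss may depend on arm or outcome.

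Size and direction are unknown. The bias runs from none to about 5.3 points, with rejection from 5% to about 15%. The upper end requires a 20% loss confined to one arm and a 65% delirium risk among those lost, all of which are assumptions. The effect on power is modest, about 2 to 4 percentage points for 5–10% loss, and it arises because 322 leaves no margin. The sample size itself is internally consistent and is not in dispute.

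**What to change.** Reword Withdrawal and dropout so that an eligibility or protocol violation does not end outcome follow-up, and only withdrawal of consent to further data collection does. State that all randomized patients complete the delirium, complication and 28-day assessments and are analyzed as allocated, and that any per-protocol analysis is a sensitivity analysis only.

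Bring three other sections into line:

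- Eligibility: say how a neuroleptic given after randomization is treated for follow-up and analysis.
- Postoperative complications: make clear that assessment to day 28 covers every randomized patient.
- Statistical analysis: define the intention-to-treat set in the same terms.

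The cost is a wording amendment, which under Protocol amendments must be agreed with the steering committee, the data safety committee, the sponsor and the funder before ethical approval, plus continued assessment of those patients who have violations. At the stated status date 60 of 322 patients had been recruited, so an early amendment would have covered the remaining 262. For patients already enrolled, sites should report whether anyone's participation was ended under the present rule and which outcomes were still obtained.

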### Confidentiality

On recruitment, the research assistant will give a unique scrambled study number to each participant. Only the study number will be used to identify participants. Data collection sheets and any printout of electronic files will be kept in a locked filing cabinet in a secure office with limited access. The master list of participants and informed consent forms will be securely stored separately from de-identified participant records. All digital files will be password protected and stored in a firewall protected secure environment. The trial sponsor has access to the final trial dataset.

### Statistical analysis

Postoperative delirium is a frequent complication after major surgery in elderly patients and is related to an increase in mortality [31]. Probability of first postoperative day PD in elderly hip fracture patients is in the range of 20–60% [9]. PD occurred in 44% of elderly patients after a major operation [31]. Our sample size was calculated to detect a 15% difference in PD between the two groups with a two-tailed test, a significance level (alpha) of 5%, and a power of 80%. The sample size calculation was performed on STATA 14.0 software (StataCorp, College Station, TX, USA). We plan to include a total of 322 participants.

Analyses will be conducted at the Clinical Research Institute of Shenzhen People’s Hospital by blinded biostatisticians. Data analysis is on an intention-to-treat basis.

The level of significance was set at 5% and statistical analysis was performed using GraphPad Prism version 6.02 for Windows (GraphPad Software, San Diego, CA, USA). Continuous variable will be summarized using means and SDs (normally distributed data) or medians and ranges (non-normally distributed data). We will perform group comparison by using the Student’s t test or Mann–Whitney test for quantitative variables and Pearson’s chi-squared test for categorical variable. The odds ratio and 95% confidence interval will be computed with logistic regression.

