## Discussion

Intraoperative MAP influences clinical outcomes [8, 9, 32]. Intraoperative hypotension has been implicated in ischemia-reperfusion injury to the brain, heart, and kidneys and is associated with death [15, 17, 20]. This multicenter, open-label, randomized, parallel-controlled clinical trial is designed to test the hypothesis that, compared with low-level MAP, high-level MAP under GA reduces postoperative complications in elderly patients during non-cardiothoracic surgery. Even a neutral result will provide an important insight, as this would mean that more studies are needed to explore a safe and effective way of blood pressure management during GA in elderly patients. This is the main strength of the present study.

There are some limitations to our study protocol. First, a multicenter design is adopted so that patients enrolled in the study include a variety of surgical procedures under different clinical environments. This will increase the generalizability of our results. Because of the apparent difference between BP management, a double-blind design cannot be achieved. Therefore, we had to use an open-label design. The following measures will be undertaken to decrease the risk of potential bias. Second, there is evidence that intraoperative BP influence long-term consequences in elderly patients after GA [33]. However, our research is primarily concerned about the effects of low-level vs. high-level MAP on short-term postoperative complications. Third, patients who will be included as eligible participants should have no cardiovascular disease and metabolic diseases. Therefore, the results of this study will be restrainedly applied to all elderly patients during non-cardiothoracic surgery under GA.

Appropriate BP management would improve patient outcomes. Strengths of the protocol include that it is the first multicenter and centrally randomized study and that it observes both the primary (the seven-day incidence of PD) and secondary endpoints (duration days of PD, intraoperative urine volume, intraoperative blood loss, specific postoperative complications, and all-cause 28-day mortality). Results of the study will provide evidence for chasing felicitous BP management in elderly patients during non-cardiothoracic surgery under GA.

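### Minor: the stated two-sample tests do not adjust day-1 laboratory values for the preoperative baseline, although the trial collects one; ANCOVA would be more precise at no cost

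*Protocol article*

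**What the plan says.** The Laboratory analyses section of the protocol article names 13 tests: AST, ALT, BUN, creatinine, CRP, CK, CK-MB, BNP, haemoglobin, white cells, platelets, oxygenation index and PaCO2. Preoperative results "performed within the last week before surgery will be used as baseline values". It continues: "Additional blood samples will be collected on postoperative day 1 for serial laboratory evaluation". The day-1 panel is not listed again. The word serial implies the same tests but does not state it.

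For continuous data the Statistical analysis section gives one general rule: "We will perform group comparison by using the Student’s t test or Mann–Whitney test for quantitative variables". The only model named is for binary outcomes: "The odds ratio and 95% confidence interval will be computed with logistic regression". No covariate and no baseline-adjusted comparison is mentioned, and the section does not say whether laboratory data enter as day-1 values or as changes.

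The Data collection section refers to "method of aggregation (for example, mean change and 95% confidence interval", but as a generic illustration that is not tied to any laboratory test.

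The outcomes after the primary one are "duration days of PD, intraoperative urine volume, intraoperative blood loss, specific postoperative complications, and all-cause 28-day mortality". No laboratory value is among them.

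**The concern.** The plan deliberately collects a baseline and a follow-up value for each marker, then states a comparison that does not use the baseline as a covariate. If the test is run on day-1 values, the between-patient variation already visible before surgery stays in the error term. If it is run on change scores, the baseline is used, but with a fixed weight that is generally not the best one.

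What is at stake is limited. The Background names brain, kidney and heart as organs sensitive to low pressure. The kidney and heart complications among the outcomes are yes/no events, in patients of ASA class I–II without cardiovascular disease or diabetes, so such events may be few. Creatinine, BUN, CK-MB and BNP are continuous blood markers for those organs and could add supporting information. A less precise comparison makes a real shift in them easier to miss.

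**Working it through.** **Inputs.** From the article: 322 patients, 1:1 allocation (161 per arm), two-sided 5%, 80% power, a 15-point difference in delirium, and a cited delirium rate of 44%. Assumed: the baseline to day-1 correlation r within arms, equal SDs at the two times, and a linear relation (after logs where needed).

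**The plan's own figure.** "Our sample size was calculated to detect a 15% difference in PD between the two groups with a two-tailed test". Taking 44% against 29% (use of the 44% is inferred, as it is the only single rate given), with pooled variance and no continuity correction:

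n per arm = [1.96·√(2 × 0.365 × 0.635) + 0.842·√(0.44 × 0.56 + 0.29 × 0.71)]² / 0.15² = (1.334 + 0.566)² / 0.0225 ≈ 160.5, rounded up to 161, so 322 in total.

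The stated size reproduces, with power 0.801 at 161 per arm. It is fixed by the binary delirium outcome, and no laboratory test enters it.

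**One laboratory marker, in units of its SD.**

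- Two-sample t test on day-1 values: (1.96 + 0.842) × √(2/161) = 0.312 SD.
- ANCOVA: multiply by √(1 − r²).
- t test on change from baseline: multiply by √(2(1 − r)).

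| Assumed r | Day-1 t test | ANCOVA | Change score | ANCOVA interval narrower than day-1 by | ANCOVA power at 0.312 SD |
|---|---|---|---|---|---|
| 0.3 | 0.312 | 0.298 | 0.369 | 4.6% | 83.6% |
| 0.5 | 0.312 | 0.270 | 0.312 | 13.4% | 89.9% |
| 0.7 | 0.312 | 0.223 | 0.242 | 28.6% | 97.5% |
| 0.8 | 0.312 | 0.187 | 0.197 | 40.0% | 99.7% |

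**Both readings of the plan.** Relative to a variance of 1 for day-1 values, ANCOVA saves 1 − (1 − r²) = r². Relative to change scores it saves 2(1 − r) − (1 − r²) = (1 − r)². Neither can be negative, so ANCOVA is at least as precise whichever way the t test is meant.

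The size of the saving differs by reading. At r = 0.7 the change score already recovers (0.312 − 0.242)/(0.312 − 0.223), about 79% of the gain in detectable difference. At r = 0.8 it recovers (0.312 − 0.197)/(0.312 − 0.187), about 92%. At r = 0.3 the change score is worse than using day-1 values alone.

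The table is for the t test. The Mann–Whitney test does not adjust for baseline either, but its detectable difference depends on the distribution and is not calculated here.

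**The case against.** The strongest case for leaving the text alone is that no listed endpoint is touched. Delirium days and intraoperative urine volume have no baseline value, the blood-loss formula already contains the preoperative haematocrit, and creatinine reaches an outcome only through the yes/no KDIGO definition of acute kidney injury. The article never spells out a between-arm laboratory comparison, and adjustment of supporting data is a detail often left to an analysis plan, which is not shown here. All of this stands and keeps the point minor. The point survives because the article does state a rule for quantitative variables, without exception, and a plan that follows the rule would carry over the less precise test.

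Four stronger readings are tempting, and the document does not support them:

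- *The plan ignores the baseline.* The text does not say so. A t test on change would use it, and mean change is mentioned, if only generically. What can be said is that neither stated test adjusts for it.
- *The comparison is biased by chance baseline imbalance.* Under randomisation the two-sample test is valid, and its 5% error rate already allows for such imbalance. The loss is precision only.
- *These markers are the only kidney and heart measures taken in everyone.* The Postoperative complications section has the assessor evaluate all participants to day 28, with criteria for kidney injury, infarction and arrhythmia, and urine volume is a secondary outcome.
- *The trial loses the equivalent of many patients.* At r = 0.5, for example, 322/(1 − 0.25) is about 429, but this describes one marker's comparison under an assumed correlation and not the trial.

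**Conclusion.** The point holds as a minor, free improvement. For laboratory tests with both values, ANCOVA is at least as precise as the stated t test, whether that test is applied to day-1 values or to changes. Against day-1 values the gain runs from slight (0.31 to 0.30 SD at r = 0.3) to substantial (0.31 to 0.19 SD at r = 0.8). Against change scores it is large only at low correlation.

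The true gain cannot be derived from the article, since no correlation is given. It will differ by marker, and a baseline taken up to a week earlier, with surgery in between, may correlate only modestly with day 1. The conclusion also assumes that the day-1 panel repeats the baseline panel. The primary analysis, the listed secondary outcomes and the sample size of 322 are unaffected.

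**What to change.** Add to the Statistical analysis section, or to the analysis plan: for each laboratory test with a baseline and a day-1 value, arms will be compared by ANCOVA of the day-1 value on arm with the baseline value as covariate. Both values will be log-transformed for skewed markers such as CK, CK-MB, BNP and CRP. The adjusted difference, or ratio on the log scale, will be reported with its 95% confidence interval. Student's t and Mann–Whitney tests remain for variables without a baseline.

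In the Laboratory analyses section, state which tests are repeated on day 1.

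The cost is a sentence or two of text, with no new data, visits or patients.
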